### *Safety outcomes*

- Skin injury (pressure or thermal) from NIRS sensor in the first 5 days after birth and adverse event reporting.

## **INTERVENTION**

After enrolment, infants will be randomised to either control group or intervention group. Monitoring of cerebral oxygenation will be commenced by using SenSmart™ Model X-100 Universal Oximetry System (from NONIN Medical Inc, MN, US) and placing a neonatal NIRS sensor on the fronto-parietal region of the infant's forehead and monitoring will be continued for 5 days (120 hours of monitoring). For the Intervention group, cerebral oxygenation reading will be visible, and the infant will be treated according to a dedicated clinical treatment algorithm when the cerebral oxygenation is outside the range of 65%–90% (see protocol).

### Intervention thresholds

A pragmatic consensus-based approach was used for selecting 65%–90% as the reference range for cerebral oxygenation. The lower threshold of 65% was chosen based on the lower threshold (55% using an adult sensor) used by the SafeBoosC-II study and higher absolute oxygenation values with neonatal sensors. A upper threshold value of 90% instead of 85% (as selected by the SafeBoosC-II study) was chosen from our local, unpublished data by monitoring preterm infants born <28 weeks gestation in the first three days of life with NONIN neonatal sensors (cerebral oxygenation of 87% was the 75th centile). The sensor site will be inspected every 4 hours to ensure correct sensor placement and skin integrity. Bedside clinicians will receive training on application of NIRS monitoring, troubleshooting advice for sensor disconnection and for technical issues.

A clinical treatment algorithm for cerebral hypoxia is triggered when cerebral oxygenation, CrSO2 is <65% (see protocol). When Cerebral oxygenation (CrSO2) is <65% potential causes include inaccurate sensor placement, low arterial oxygen saturation, reduced cerebral blood flow or reduced haemoglobin concentration in circulating blood. A clinical treatment algorithm for cerebral hyperoxia is triggered when cerebral oxygenation, CrSO2 is >90% (see protocol). When cerebral oxygenation (CrSO2) is >90% potential causes include inaccurate sensor placement, high arterial oxygen saturation, increased cerebral blood flow, or hypoglycaemia.

For the control group, cerebral oxygenation reading will not be visible to the bedside staff and the infant will be treated according to standard clinical practice. We will perform blinded NIRS monitoring by covering the monitor screen with an opaque cover and the information will not be available to clinicians to act upon.

## **RANDOMISATION AND BLINDING**

Central randomisation will be performed by the site investigator or the medical team member using REDCap electronic data capture tools hosted at University of Sydney. Infants assessed as eligible will be randomised to control group or intervention group by using variable block randomisation stratified for gestation age (<26 weeks' and  $\geq 26$  weeks') and study site. Randomisation codes for the study will be generated by a biostatistician independent to the study. Permuted blocks will maintain group balance, infants will be allocated to two groups in a 1:1 ratio. Twins will be randomised to the same group, based on negligible intra-class coefficient burden of hypoxia within pairs of twins in SafeBoosC-II study and survey of parents of multiple births.

To ensure concealment, the block sizes will not be disclosed. Additionally, allocation concealment will be ensured, as REDCap will not reveal the randomisation until the infant has been recruited into the trial. REDCap will maintain a list of participants enrolled. Each site investigator/s will access only to their site records. The chief investigators will have access to all sites to oversee enrolment. Participants will be given unique codes to protect their identity on all documentation utilised for recording and analysis purposes. Separate data records will be maintained for re-identifiable and de-identified data.

### **Blinding (masking)**

During the intervention period, the assignment of infants to control arm or intervention arm cannot be blinded to the clinical staff. For infants in the control arm, blinding will be performed by covering the NIRS monitor screen with an opaque cover. Also, alarms for the range of cerebral oxygenation (65%–90%) will be turned off and alarms for displacement/dislodgement of the sensors will remain active. The statistician and neurodevelopment outcome assessors will be blinded to the intervention.

## **SAMPLE SIZE**

Based on the results of the Safe-BoosC-II study, a 50% reduction in mean burden of hypoxia and hyperoxia in active treatment relative to control would be considered worthwhile. This corresponds to a reduction of 0.3 in the mean of log-transformed burden of cerebral hypoxia and/or hyperoxia. In the Safe BoosC-II study, a 58% reduction was achieved. Assuming a standard deviation of 0.5 in log-transformed burden, this would require 45 babies per group to achieve 80% power at 5% two-sided alpha. To account for the clustering effect of twins being allocated to the same treatment, we assume that 30% of babies are twins-based on regional incidence of twin births (giving an average cluster size of 1.3, and a within-twin correlation of 0.1 in the outcome. This gives a design effect of 1.03 by which the sample size is adjusted, leading to a sample size of 47 per group, 94 babies in total. We aim to recruit 100 babies to account for some loss to follow-up or missing data. For consented participants, if the NIRS monitoring was discontinued earlier than 5 days after birth, data collected until discontinuation of monitoring will be used for analysis of the primary outcome.

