We believe that prior to conducting a large multisite international RCT investigating the impact of using a combination of cerebral NIRS monitoring and dedicated clinical treatment guideline on composite outcome of death before hospital discharge and neuro-developmental outcome at 2 years corrected age, it is important to conduct a phase II RCT incorporating important differences to SafeBoosC – II study. It is important to investigate if a significant difference truly exists by following a dedicated conservative clinical guideline combined with cerebral oxygenation monitoring (intervention group) versus treatment as usual and blinded cerebral oxygenation monitoring (control group).

*Table 1 Data from previous RCT of cerebral oxygen targeting in preterm infants*

| Outcome                                                       | NIRS guided algorithm | Placebo           | Risk Ratio (95%CI)  | P value (unadjusted) | P value (adjusted) |
|---------------------------------------------------------------|-----------------------|-------------------|---------------------|----------------------|--------------------|
| Median (IQR) burden of hypoxia and hyperoxia (% hours) | 36.1 (9.2-79.5)       | 81.3 (38.5-181.3) | -58 (-35 to -74)    |                      | < 0.001            |
| All-cause mortality, n (%)                             | 12/86 (14)            | 20/80 (25)        | 0.50 (0.29 to 1.00) | 0.049                | 0.10               |
| Brain Injury on US, n (%)                              |                       |                   |                     | 0.053                | 0.11               |
| None                                                          | 21/80 (26)            | 26/77 (34)        |                     |                      |                    |
| Mild-Moderate                                                 | 49/80 (61)            | 33/77 (43)        |                     |                      |                    |
| Severe                                                        | 10/80 (13)            | 18/77 (23)        |                     |                      |                    |
| Necrotising enterocolitis, n (%)                       | 9/86 (11)             | 10/80 (13)        | 0.83 (0.33 to 1.94) |                      | 0.69               |

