| Motor performance                                |           |            |              |    |    | X  |    | X  |    |    |    |
| Neuro-developmental follow up                    |           |            |              |    |    |    |    | X  | X  | X  | X  |

**T1** =Post-allocation to 5 days from birth; **T2** = first week from birth; **T3** = 32 weeks PMA or 6 weeks after birth; **T4** = 36-37 weeks PMA; **T5** = term PMA (37-40 weeks); **T6** = Follow-up assessment at 3-4 months corrected age, **T7** = 12 months corrected age, **T8** = 18-24 months corrected age, **T9** = 5 years of age.

402

403

404

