### Outcomes

| Tool                 | Outcomes                                                                                                                                            | Time points                                                                   |
|-----------------------------|------------------------------------------------------------------------------------------------------------------------------------------------------------|--------------------------------------------------------------------------------------|
| Cerebral NIRS monitors      | Burden of hypoxia and hyperoxia expressed as percentage time spent < 65% and > 90%.                                                                        | First 5 days of monitoring period                                                    |
| Medical records             | Mortality rates                                                                                                                                            | Prior to home discharge                                                              |
| Cerebral imaging            | Evidence of brain injury on cranial ultrasounds and MRI brain (when performed for clinical reasons)                                                        | Prior to home discharge                                                              |
| Medical records             | Presence of neonatal morbidities (chronic lung disease, necrotizing enterocolitis, retinopathy of prematurity)                                             | Prior to home discharge                                                              |
| Neuro-developmental testing | 

General movement assessment

Cognition, motor and language domain scores on Bayley Scales of Infant

 | At 4 months (CGA)

At 12 months (CGA), 18-24 months (CGA), and 5 years of age. |

|                                 |                                                                                                                                  |                                   |
|---------------------------------|----------------------------------------------------------------------------------------------------------------------------------|-----------------------------------|

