## **OUTCOMES**

### *Primary outcome*

- The burden of cerebral hypoxia and hyperoxia during the first 5 days expressed as percent hours.

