### *Analysis of the outcomes*

Participant demographic and clinical characteristics and study outcomes will be presented using standard descriptive statistics: frequencies and percentages for categorical variables, mean, standard deviation and range or median, quartiles and range for continuous variables. All efficacy analyses will be performed according to randomized treatment. We will use a suitable transformation to ensure normality for the primary outcome, the burden of cerebral hypoxia and hyperoxia and use generalized estimating equation (GEE) or a similar method for comparison between groups. Sub-group analysis for stratification variables will be performed. For reporting the burden of cerebral hypoxia and hyperoxia, we will include deviations in cerebral oxygenation more than a minute. This pragmatic approach will ensure we achieve a balance between responding to an alarm from poor sensor contact with the participant and identifying true real-time changes in cerebral oxygenation. To allow comparison of the primary outcomes with other studies, we will also report the burden of cerebral hypoxia and hyperoxia more than 10 minutes. Other study outcomes will be compared using similar methods, using GEE methods with normal or binary outcome distribution and correlation between outcomes in twins. Adjusted models will explore predictors out outcomes. No corrections for multiple hypotheses will be performed. Adjusted models will be used to explore predictors of outcomes. Variables that differed significantly between the two groups, and could plausibly contributory to the outcome, will be considered for adjustment. A fixed adjustment for gestational age category will be included as an a priori specified variable. For this trial, no imputation of missing data will be performed and sensitivity analysis will only be performed separately for the burden of cerebral hypoxia and cerebral hyperoxia. In future, sensitivity analysis may be performed for variables such as specific gestational age or treatment received.

Withdrawn participants will be replaced in the study with new randomisation (per protocol). To facilitate and ensure long term follow up, existing measures which are standard practices includes providing appointment letters by post, reminding and confirming with families by phone and/or text message when follow up appointment is close to date.

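### The primary outcome has no stated denominator, so recordings that stop early may score mechanically low

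*Combined protocol and SAP*

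**What the plan says.** The primary outcome is described in two ways. Protocol section 5.4 and the SAP (Primary outcome) have "The burden of cerebral hypoxia and hyperoxia during the first 5 days expressed as percent hours". The outcomes table in protocol section 6.5 has "Burden of hypoxia and hyperoxia expressed as percentage time spent < 65% and > 90" per cent. Neither gives a formula or a denominator.

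For recordings that stop early, the SAP (Sample size) says of consented participants that "data collected until discontinuation of monitoring will be used for analysis of the primary outcome". The SAP (Analysis of the outcomes) adds that "no imputation of missing data will be performed and sensitivity analysis will only be performed separately for the burden of cerebral hypoxia and cerebral hyperoxia". The SAP (Statistical analysis, data cleaning) also deletes readings of 0 and 100.

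The planned window is given in two forms. The SAP (Intervention) says "monitoring will be continued for 5 days (120 hours of monitoring" in total. The footnote to the schedule table in protocol section 6.2 defines the intervention period as "Post-allocation to 5 days from birth".

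**The concern.** A burden that accumulates over time depends on how long it is recorded. If a truncated recording is entered without scaling, each unrecorded hour counts as an hour with no burden. This applies whether the hour was lost because monitoring stopped, the sensor lost contact or readings were deleted. Two infants with the same oxygenation pattern would then get different primary outcome values because one was recorded for longer.

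Any difference between arms in recorded time would pass into the treatment comparison. The exploratory objective relating burden to mortality (protocol section 5.3) would be affected too: for a consented infant who dies early, death itself would shorten the exposure meant to be related to it.

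Because the two descriptions of the outcome differ, two analysts could derive different primary results from the same files, and nothing in the plan says which is intended.

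**Working it through.** **Inputs.** From the SAP (Sample size): target difference 0.3 on the log scale (a 50% reduction), SD 0.5, two-sided alpha 5%, power 80%, design effect 1.03, 47 per group. From the SAP (Intervention): 120 hours. From protocol Table 1: control burden in the earlier trial, in % hours, of "81.3 (38.5-181.3" (median, then quartiles). Assumed here, because the documents do not give them: a constant burden rate, the share of infants who stop early, and the hour at which they stop.

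**1. The plan's own figure.** log10(0.5) = -0.301, so the log is base 10. The normal approximation gives n = 2 x [0.5 x (1.960 + 0.842) / 0.3]^2 = 43.6, or 44 per group. The t-based calculation gives 45 (power 0.804). 45 x 1.03 = 46.35, rounded up to 47, so 94 in total. The stated sample size reproduces.

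**2. What the unit can mean.** The upper quartile of 181.3 exceeds 100, so in Table 1 percent hours is not a share of time. It looks like a cumulative total, but Table 1 does not show whether that total was scaled to a fixed window. For this trial three readings remain open:

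| Reading | Effect of a short recording |
|---|---|
| Cumulative total, unscaled | mechanically low |
| Share of the planned 120 h | mechanically low |
| Share of (or rate per) recorded hour | no mechanical shift |

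**3. Shift for one infant, first two readings.** At a constant rate the log10 shift is log10(h/120):

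| Hours recorded | Share of full value | log10 shift |
|---|---|---|
| 96 | 0.80 | -0.097 |
| 72 | 0.60 | -0.222 |
| 60 | 0.50 | -0.301 |
| 48 | 0.40 | -0.398 |
| 24 | 0.20 | -0.699 |

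**4. Shift in the arm comparison.** Bias in the mean log difference = (difference in stopping share) x (shift per infant). The apparent ratio is the true ratio of 0.5 times or divided by 10^bias, according to which arm stops more.

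| Difference in stopping share | Hour of stopping | Bias (log10) | Factor | More stopping in controls | More stopping in intervention |
|---|---|---|---|---|---|
| 10 points | 48 | 0.040 | 1.096 | 0.548, a 45% reduction | 0.456, a 54% reduction |
| 5 points | 60 | 0.015 | 1.035 | 0.518, 48% | 0.483, 52% |
| 5 points | 24 | 0.035 | 1.084 | 0.542, 46% | 0.461, 54% |

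With no true effect, the first row would show a spurious difference of 9 to 10%.

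**5. Against the precision of the trial.** Standard error = 0.5 x sqrt(2 / (47/1.03)) = 0.105. The bias of 0.040 is about 0.4 standard errors.

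**6. Equal stopping in both arms.** The mean bias is zero, but the spread grows: the variance becomes 0.25 + p(1-p) x shift^2. With p = 10% in each arm, power falls from 0.818 to 0.805 (stop at 60 h) or 0.753 (stop at 24 h).

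**7. The two windows.** If monitoring starts at the 6-hour limit and ends 5 days from birth, it lasts 114 hours, and log10(114/120) = -0.022. This is small.

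**The case against.** The strongest answer is the outcomes table in protocol section 6.5. If the outcome is a share of recorded time, a short recording has no mechanical shift, and deleted 0 and 100 readings simply leave the denominator. That is right as far as it goes, and a reader who infers that shortened recordings certainly score falsely low goes beyond the documents. But the table names no denominator, and it conflicts with the percent-hours wording elsewhere.

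The role of death is also narrower than it may seem. The early-stopping rule covers consented participants and does not mention death. Under protocol section 7.4, an infant who dies before the parents can be approached has all data removed. That is a separate selection issue. Only infants already consented, for example antenatally under section 7.1, can enter with a recording cut short by death. Nor does such an infant necessarily look better than a survivor: a short recording covering an unstable period could score high.

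The size can be overread in two ways. The mortality of 14% against 25% in Table 1 has no stated time window, so it does not give stopping rates for the first 5 days. If stopping did follow that pattern, with more in controls, the bias would be towards no effect. Also, the -0.40 shift belongs to one infant and should not be set against the 0.3 difference in group means. Protocol section 8.3 calls withdrawal after consent extremely uncommon, which argues for small differences between arms. These points limit the likely bias but do not supply the missing definition.

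**Conclusion.** The concern holds as a conditional one. The sole primary outcome has two conflicting descriptions, no formula and no denominator. Incomplete recordings enter as they stand, and no planned analysis would reveal or correct an effect of recording length. The percent-hours wording, read with the values above 100 in Table 1, points towards a cumulative total, but the documents do not settle it.

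On an unscaled reading, a recording that stops at 60 hours loses 0.30 on the log10 scale for that infant, and one that stops at 48 hours loses 0.40. For the arm comparison, an assumed 10-point difference in stopping at 48 hours moves a true 50% reduction to about 45% or 54%, roughly 0.4 standard errors. The direction is not fixed, and equal stopping leaves the mean comparison unbiased. These figures rest on a constant burden rate and on stopping rates that the documents do not give. The difference between 120 and 114 hours matters only as something to reconcile.

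The choice of denominator should be fixed before unblinding.

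**What to change.** In the SAP, define the primary outcome for every infant as out-of-range burden divided by valid recorded hours, scaled to the planned window (for example, times 120). Write the numerator out in full. State that deleted 0 and 100 readings and sensor gaps are excluded from the denominator.

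Bring these sections into line with that definition: protocol section 5.4, the schedule footnote in section 6.2, the outcomes table in section 6.5, and the SAP headings Primary outcome, Intervention and Sample size. Say explicitly how the definition applies to consented infants who die during monitoring.

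Report valid recorded hours by arm. Add one sensitivity analysis by recording length, and amend the SAP sentence that limits sensitivity analyses to hypoxia and hyperoxia separately.

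The cost is a few sentences and one extra model run. No new data are needed and the sample size does not change. Under a constant rate the mechanical shift becomes zero at every recording length. The downside is that a rate assumes unrecorded hours resemble recorded ones, which may fail when monitoring stops because the infant is deteriorating; the hours by arm and the sensitivity analysis let a reader judge how much depends on it.

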## **STATISTICAL ANALYSIS**

Analysis will be conducted per-protocol using RStudio.Version(4) at a significance level of 0.05 with a two-sided alternative hypothesis. The reporting will adhere to the CONSORT guidelines.

Data cleaning: In absence of international guidelines on handling NIRS artifacts, the artifacts will be included in the data analysis. Extreme values for cerebral oxygenation (0 and 100) will be removed.

### *Interim analysis*

There will not be an interim analysis. The Data and Safety Monitoring Board's first meeting will be 6 months from initial recruitment and will continue every 6 monthly until end of recruitment. A review of the study by the data and safety monitoring board will be performed.

### *Analysis of the outcomes*

Participant demographic and clinical characteristics and study outcomes will be presented using standard descriptive statistics: frequencies and percentages for categorical variables, mean, standard deviation and range or median, quartiles and range for continuous variables. All efficacy analyses will be performed according to randomized treatment. We will use a suitable transformation to ensure normality for the primary outcome, the burden of cerebral hypoxia and hyperoxia and use generalized estimating equation (GEE) or a similar method for comparison between groups. Sub-group analysis for stratification variables will be performed. For reporting the burden of cerebral hypoxia and hyperoxia, we will include deviations in cerebral oxygenation more than a minute. This pragmatic approach will ensure we achieve a balance between responding to an alarm from poor sensor contact with the participant and identifying true real-time changes in cerebral oxygenation. To allow comparison of the primary outcomes with other studies, we will also report the burden of cerebral hypoxia and hyperoxia more than 10 minutes. Other study outcomes will be compared using similar methods, using GEE methods with normal or binary outcome distribution and correlation between outcomes in twins. Adjusted models will explore predictors out outcomes. No corrections for multiple hypotheses will be performed. Adjusted models will be used to explore predictors of outcomes. Variables that differed significantly between the two groups, and could plausibly contributory to the outcome, will be considered for adjustment. A fixed adjustment for gestational age category will be included as an a priori specified variable. For this trial, no imputation of missing data will be performed and sensitivity analysis will only be performed separately for the burden of cerebral hypoxia and cerebral hyperoxia. In future, sensitivity analysis may be performed for variables such as specific gestational age or treatment received.

Withdrawn participants will be replaced in the study with new randomisation (per protocol). To facilitate and ensure long term follow up, existing measures which are standard practices includes providing appointment letters by post, reminding and confirming with families by phone and/or text message when follow up appointment is close to date.

This trial will be conducted in accordance with applicable Privacy Acts and Regulations in all three countries. Data will be stored for a minimum of 15 years or until the youngest participant turns 25 (whichever is the longest).
